### Health economic analysis

A full cost-effectiveness analysis will not be undertaken as part of the current study. Rather, the work will identify the feasibility of collecting the data, needed for an economic analysis of a full-scale trial. Health service resource use will be collected from participants using a bespoke questionnaire that will include items such as hospital attendances and admissions and also primary care visits (eg, GP, physiotherapist and prosthetist). The costing approach will be undertaken from an NHS perspective and unit costs will be derived from established national costing sources such as NHS Reference Costs^30^ and Personal Social Services Research Unit costs of health and social care.^31^ The costs of providing the novel prosthesis will be estimated and the potential resource implications versus the standard prosthesis will be explored.

### Safety measurements

Adverse events (AEs) related to the prosthesis only, and any serious adverse event (SAE), will be recorded throughout the study. Intensity and relationship to the study intervention will be described. Ongoing review of AEs and SAEs will take place during monthly Trial Management Group (TMG) meetings, discussed with the Patient Advisory Group (PAG) and Trial Steering Committee (TSC), and reported to the sponsor and ethics committee in line with their guidelines. Participants may withdraw from the study at any time without influencing their future care or treatment.

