In order to clearly identify an amputee’s current and potential functional status the insurance group, Medicare, established Medicare Functional Classification Levels (also called K levels) in 1995, which is widely used internationally. It is a method of quantifying need and the potential benefit of prosthetic devices for those with a lower limb amputation. Five classification levels (K0: low functional level to K4: high functional level) were established.^12^ An alternative classification system is the SIGAM (Special Interest Group in Amputee Medicine) developed by the British Society of Rehabilitation Medicine which measures levels of mobility (grade A: lowest mobility to grade F: highest mobility).^13^ A self-aligning prosthesis has been designed specifically for the K2 user, categorised as ‘limited mobility’, to alleviate many of the patient-reported limitations of a standard prosthesis. This prosthesis adjusts to slopes and steps via hydraulic mechanisms. A self-aligning prosthesis can improve ground clearance to avoid a fall, and aligns to secure the biological knee in individuals with a transtibial amputation, which is important for falls prevention.^14^ Based on laboratory studies, this type of self-aligning prosthesis also has demonstrated reduced residuum-socket interface pressures,^15^ which could alleviate pain in the residuum longer term. Although a self-aligning prosthesis is more expensive than a standard prosthesis (by approximately £800), the potential patient benefits through increased mobility, quality-of-life and fewer falls could offset future healthcare and socioeconomic costs. Previous studies have shown that more functional prostheses may offer better patient function and improve mobility in people with a lower limb amputation.^16 17^ However, these studies have not been undertaken in older patients and therefore have not considered the health comorbidities that affect older, often vascular, patients compared with younger, more active amputees.

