### Blinding

By the nature of the interventions used within this study, blinding of the participants and investigators is not possible and procedures for breaking codes/unblinding are not necessary.

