### Outcome measures

Table 1 details the information to be collected according to time points. The participant questionnaires include the following.

Locomotor Capabilities Index-5.^20^

**Table 1 T1:** Trial activity and data collection time points

	Screening	Baseline assessment (in clinic)	Prosthetic fitting (weeks 1–3)	Week 9 follow-up assessment (postal)	Week 15 assessment (postal)	Week 16 follow-up assessment (in clinic)
Eligibility screening form	**X**					
Consent		**X**				
Questionnaires						
Demographics		**X**				
LCI-5		**X**		**X**		**X**
Houghton		**X**		**X**		**X**
EQ-5D-5L		**X**		**X**		**X**
PROMIS 3a ānd 8a		**X**		**X**		**X**
Healthcare resource use		**X**		**X**		**X**
Clinical assessments						
2mWT		**X**				**X**
TUG		**X**				**X**
TUDS		**X**				**X**
BBS		**X**				**X**
1 week activity monitor		**X**			**X**	
Novel prosthesis treatment group only			**X**			

BBS, Berg Balance Scale; LCI-5, Locomotor Capabilities Index-5; PROMIS, Patient-Reported Outcomes Measurement Information System; TUDS, Timed Up and Down Stair test; TUG, Timed Up and Go test; 2mWT, 2 min walk test.

Houghton Scale—prosthetic use in people with lower extremity amputations.^21^
Patient-Reported Outcomes Measurement Information System (PROMIS) Short-Form v1.0 Pain (3a and 8a) questionnaires.^22^
EQ-5D-5L.^23^
Bespoke health resource use questionnaire.

The four clinical assessments will be carried out at baseline with the participant wearing their standard prosthesis and repeated at final follow-up, wearing whichever prosthesis they are using at the time. Participants may also use their regular walking aid and choose not to attempt some assessments. The assessments are as follows.

2-min walk test.^24^
Timed-Up and Go test.^25^
Timed-Up and Down test.^26^
Berg Balance Scale.^27^

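### Recording non-serious adverse events only when they are prosthesis-related may capture falls and skin problems differently by arm in this open trial, and no fall count is listed as an outcome

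*Protocol article*

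**What the plan says.** The protocol article, under Safety measurements, sets the recording rule: "Adverse events (AEs) related to the prosthesis only, and any serious adverse event (SAE), will be recorded throughout the study". It continues: "Intensity and relationship to the study intervention will be described". It does not name who decides relatedness. It also does not say whether the prosthesis in the rule means whichever device the participant is wearing or only the novel one.

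Under Blinding it says that "blinding of the participants and investigators is not possible".

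Under Intervention and standard treatment, the novel arm has a fitting appointment and an offer of physiotherapy where clinically needed. The standard arm keeps its existing foot and its usual care. Both arms receive the week-9 postal questionnaire and attend the final clinic assessment (Study visits and follow-up).

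The Introduction uses falls to justify the device: "A self-aligning prosthesis can improve ground clearance to avoid a fall", and "the potential patient benefits through increased mobility, quality-of-life and fewer falls could offset future healthcare and socioeconomic costs".

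Under Outcome measures, "Table 1 details the information to be collected according to time points". The list is LCI-5, Houghton, PROMIS pain 3a and 8a, EQ-5D-5L, resource use, four clinical tests and the activity monitor. The Health economic analysis section describes the resource-use questionnaire as covering "items such as hospital attendances and admissions and also primary care visits". Falls are named in neither place.

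**The concern.** A relatedness judgement made after an event is logged can be reviewed, repeated or ignored in analysis. One made before logging cannot, because the unrelated events are never written down. In an open trial, a stumble or a sore on a newly fitted foot may prompt the thought that the foot caused it more readily than the same event on a foot worn for a year or more. The novel arm also has more occasions on which an event can come up. Either mechanism could make the recorded counts differ when the true counts do not.

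The second part concerns purpose. Under Aim and objectives, the trial is to identify a primary outcome for the main trial and to assess completeness of follow-up data. Falls are one of the benefits claimed for the device, but a non-serious fall reaches the dataset as an event only if someone attributes it to the prosthesis. The trial would then finish without a fall rate and without knowing whether falls can be collected in this population.

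**Working it through.** **The plan's own figure.** The only relevant number is the sample size: 72 / (1 − 0.20) = 90, which reproduces. With 1:1 allocation that is 90 / 2 = 45 per arm. The plan gives no event rates or attribution probabilities, so everything numerical below is assumption.

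**What passes the filter.** Reading the sections together:

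| Event | Route into the data | Depends on relatedness? |
|---|---|---|
| Any serious event, including a serious fall | Safety measurements | No |
| Pain | PROMIS 3a and 8a, both arms, baseline, week 9 and final | No |
| Balance and mobility function | Berg Balance Scale, Timed Up and Go and other tests | No, but these do not count falls |
| Health service contact after a fall | Resource-use questionnaire | No, but falls are not named |
| Non-serious fall | Adverse event record only | Yes |
| Non-serious residual-limb skin problem | Adverse event record only | Yes |

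The gap is the last two rows.

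**How large could differential recording be?** Let the true risk of a non-serious event be the same in both arms, and let attribution be the probability that such an event is called prosthesis-related.

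Expected recorded participants = 45 × true risk × attribution.

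| Attribution, novel v standard | True risk 20% | True risk 40% | Ratio |
|---|---|---|---|
| 80% v 80% | 7.2 v 7.2 | 14.4 v 14.4 | 1.00 |
| 80% v 60% | 7.2 v 5.4 | 14.4 v 10.8 | 1.33 |
| 80% v 40% | 7.2 v 3.6 | 14.4 v 7.2 | 2.00 |
| 90% v 30% | 8.1 v 2.7 | 16.2 v 5.4 | 3.00 |

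Example: 45 × 0.20 × 0.80 = 7.2 and 45 × 0.20 × 0.40 = 3.6, so the ratio is 0.80 / 0.40 = 2.0. The corresponding false difference is 0.20 × (0.80 − 0.40) = 8 percentage points.

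The ratio depends only on the two attribution probabilities. It does not change with the true risk or with attrition that is equal in the two arms. Swapping the attribution columns reverses the direction. Equal attribution gives no distortion between arms, although the absolute rate is still understated: at 80% in both arms, 7.2 recorded against 45 × 0.20 = 9.0 true.

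**Can the design detect which row applies?** Not from the measures listed. Table 1 has no unfiltered count of falls or skin problems in either arm against which the adverse event record could be compared.

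**The case against.** Several stronger readings are tempting, and the document does not support them.

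- *That events will be captured unequally.* The rule is worded identically for both arms. Unequal capture is permitted by the text but not established by it, and its direction is not known.
- *That unblinded staff make the judgement.* The Safety measurements section names no assessor. What can be said is that participants and investigators know the allocation.
- *That key safety events are lost.* The same sentence says "and any serious adverse event (SAE), will be recorded throughout the study" for serious events, with no relatedness condition.
- *That residual-limb pain is also unmeasured.* PROMIS pain scores are collected from both arms. They are not specific to the residual limb, but they do not pass through the filter.
- *That the standard arm has only usual-care contact.* Both arms share the week-9 questionnaire and the final clinic visit. The difference is a fitting visit and optional physiotherapy.

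The broader defence also has weight. The device is already on the market and prescribable in the NHS, the trial is described as low risk, no formal analysis between arms is planned, and the patient involvement work helped choose the outcomes. Targeted recording of adverse events can be a reasonable choice in that setting. The full protocol and case report forms, not shown, may define the assessor and the method of elicitation, and the resource-use list is given as examples only.

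These arguments limit the consequence but do not remove the point. The filter and the outcome list are positive statements in the article, not details left out of it. Descriptive counts still feed the safety review and main-trial planning. If the patient-facing work shows that falls matter to participants, the listed measures will provide no fall rate or completeness figure to go with that finding.

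**Conclusion.** The point holds in a limited form. For non-serious falls and residual-limb skin problems, a relatedness condition applied before recording, in an open trial where one arm alone receives a new device and extra contacts, allows recording to differ by arm in a way no analysis can undo. Separately, falls are part of the rationale and cost case, but no fall count is listed. The feasibility trial therefore cannot report a fall rate or fall-data completeness when the main-trial outcome is chosen.

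The size of any differential recording is unknown. Under the assumed attribution splits above, the recorded ratio runs from 1.0 to 3.0, and it is exactly 1.0 if attribution is equal. Those splits and the 20% and 40% risks are illustrations, not estimates. Serious events and pain scores are unaffected. This is a cheap improvement to make, not a flaw that undermines the trial's feasibility aims.

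**What to change.** Add the same short items on falls and residual-limb skin problems, with the same fixed recall period in both arms, to the baseline, week-9 and final questionnaires that every participant already receives. Record what is reported whether or not anyone attributes it to the prosthesis, and classify relatedness afterwards as a separate field. In the Safety measurements section, state who makes that classification and which device it refers to in each arm. Report counts and item completeness descriptively, by arm as randomised.

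The cost is an ethics amendment, slightly longer questionnaires for participants, and more non-serious events to log. No extra visit is needed. Participants who have already completed a questionnaire will lack the items for that time point, so report completeness with the number who were actually asked as the denominator.

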### Trial monitoring and oversight

Due to the low risk nature of this trial, there will be one independent steering and monitoring committee to undertake the roles traditionally undertaken by the TSC and Data Monitoring and Ethics Committee. This Trial Steering and Monitoring Committee will comprise of independent members including a Chair, a statistician, one other independent person, and a member of the PAG.

The TMG, comprising the chief investigator, the York Trials Unit and coinvestigators, will provide overall management of the study. York Trials Unit is responsible for project management. We will establish a PAG with between four and eight members that will meet a minimum of five times over the duration of the project. The PAG is a group of independent patients with an amputation and their carers, whose role is to support and advise the TMG on all aspects of the study and to facilitate its progress and management.

### Patient and public involvement

Three funded patient and public involvement (PPI) events were carried out at the recruiting sites to inform the development of this study. The PPI events helped to identify the objectives for the feasibility study, specify outcomes that are significant to this patient population, and share views on the randomisation process. This has enabled the team to prioritise outcome measures related to amputee patient function and well-being, and explore how to introduce the study to potential participants while taking into account their valid concerns about randomisation.

### Data collection, integrity and management

Data will be collected through paper questionnaires identified by a unique identification number only (ie, the participant identification number in all manual and electronic files). Each site will hold data according to the General Data Protection Regulation (May 2018). A Trial Enrolment Log at the sites will list the participant identification numbers. York Trials Unit will maintain a list of participant identification numbers for all trial patients at each site.

All paper documents will be stored securely. All information collected will be stored on a secure password-protected server located at the University of York, for the purpose of assisting in follow-ups during the study and will be kept strictly confidential.

The confidentiality of participants and staff interviewed during the qualitative interviews will be ensured by assigning a unique participant number to electronic sound files and transcripts, known only to the qualitative researcher and appropriate members of the research team. Any quotes published will be anonymous. All data collected will be archived for ten years following the end of the study.

### Ethics and dissemination

Yorkshire and The Humber—Leeds West Research Ethics Committee granted ethical approval for this study on 4 May 2018. Since the study started, the Health Research Authority approved three substantial amendments to the protocol which are included in the final version reported here.

Inclusion of clear written and pictorial instructions for fitting the activity monitor to the participant’s prosthesis.Alteration to the recruitment process such that staff at the local prosthetics centre could contact a potential participant after invitations packs had been sent to them.Inclusion of a cover letter to accompany the participant information sheet for the qualitative interview aspect of the study.

The proposed study will be conducted in accordance with the Medical Research Council Guidelines on Good Clinical Practice in Clinical Trials.

The results will inform the design and delivery of a definitive RCT. The findings from this study will be presented to relevant groups such as the British Association of Chartered Physiotherapists in Amputee Rehabilitation (BACPAR) and the British Association of Orthotists and Prosthetists (BAPO). Participants will be informed of the outcome of the study. With the help of our PAG representatives, the findings will be disseminated to participants, other patients and their carers, and relevant patient support groups, including national charities supporting individuals following limb loss. The results will also be submitted to the funders, peer-reviewed journals, presented at relevant meeting/conferences, including participating recruitment sites.

## Conclusion

There is limited robust evidence about the benefits of prescribing a self-aligning prosthesis for patients over the age of 50 years, who are predominantly prescribed a standard (ie, more rigid) prosthesis. The outcomes from this study will inform a larger fully powered RCT designed to determine the effectiveness of a self-aligning prosthesis in improving a patient’s daily mobility.
